### Concealment mechanism {16b}

As the allocation is done during questionnaires by the software SoSci Survey, sequences are unknown to both researchers and participants.

### Implementation {16c}

Both generation of the allocation sequence and assignment to the intervention groups is executed by a computer system. Participants are enrolled by the lead investigator (GM), who does not know the allocation sequence.

## Assignment of interventions: blinding

### Who will be blinded {17a}

Trial participants are blinded throughout the study. Statistical analysis will be executed by generating a number for each group, with its affiliation unknown to the analyst.

### Procedure for unblinding if needed {17b}

Due to anonymization, unblinding is not possible. Researchers have minimal contact with participants during the trial and potential harms are unlikely due to the non-invasive psychological nature of the trial.

## Data collection and management

### Plans for assessment and collection of outcomes {18a}

#### Primary outcome—interpersonal emotion regulation

Vignettes [39] are used to depict short sequences of events and have been successfully used in psychological research (e.g. [40]). While often consisting of short written text, we will use visual vignettes [41] (to reduce reading for the participants and to be able to show emotional expressions) with hypothetical situations that require the use of iER before and after the game to assess if children’s perception of their options have changed, i.e. if they can think of more strategies to help a person in a hypothetical situation after they have played the iER AG. A visual scene will depict an every-day life situation with a person experiencing a negative emotion that needs to be regulated. Every participant will receive the same four different scenarios, containing 1 image depicting the scene (Table 3). For each scenario, participants get an open-ended question (“If you were in that room, what could you do in this situation to help this person? Write down everything you can think of.”).

**Table 3 Tab3:** Vignette task for interpersonal emotion regulation strategies

	Scenario	Emotion
1.	An early adolescent trips over in front of their peers.	Embarrassment
2.	An early adolescent is scared of a spider.	Fear
3.	An early adolescent is being excluded by their peers.	Sadness
4.	An early adolescent is angry because someone broke their phone.	Anger

#### Secondary outcomes

*Emotion regulation skills*. The Emotion Regulation of Others and Self scale (EROS [42];) will be used to measure both personal and interpersonal ER. This scale includes four factors of ER: intrinsic (personal) affect-improving, intrinsic affect-worsening, extrinsic (interpersonal) affect-improving, and extrinsic affect-worsening and shows good internal reliability and construct validity. Of the overall 19 items, 9 measure extrinsic (interpersonal) ER and 6 extrinsic affect-improving ER. The instructions ask to report the extent the person had used the strategy over the past 4 weeks to try to change their own or someone else’s feeling on a five-point Likert scale (“not at all”, “just a little”, “moderate amount”, “quite a lot”, “a great deal”). One example item is: “I listened to someone’s problem.”. The mean score in an adult population for extrinsic affect-improving is 3.53, for extrinsic affect-worsening 1.20. Internal consistency ranges from *α* = 0.74 to *α* = 0.82. The measure will be translated into German according to standard recommendations for the translation and adaptations of questionnaires [43].

*Emotional competence*. To measure emotional competence in early adolescents, the Emotional Skills and Competence Questionnaire (ESCQ [44];) will be used. The questionnaire consists of 45 items on three subscales: the Perceive and Understand emotions scale (15 items; e.g. “When I see how someone feels, I usually know what has happened to him”), the Express and Label emotions scale (4 items; e.g. “I am able to express my emotions well.”), and the Manage and Regulate emotions scale (16 items; e. g. “When I am in a good mood, every problem seems soluble”). Ratings are given on a 5-point scale (“never” to “always”). Internal consistency ranged from α = .81 to .90 (Perception and Understanding), .78 to .88 (Express and Lable), and .67 to .78 (Manage and Regulate), and .88 to .92 (overall emotional competence). The measure will be translated into German by the same procedure as described before.

*Sex differences*. Sex differences will be examined in the experimental subgroup of our sample. During gameplay, the player undergoes 10 different scenarios, where they interact with NPCs by choosing one of up to four dialogue options. The four different strategies according to Niven, Totterdell [4] will be presented during these interactions. The dialogue options will consist of two adaptive and two maladaptive strategies (on average, with a range of 2–4 adaptive options, but always including both strategies of “positive engagement” and “acceptance”). Each picked option will be saved by the game, compiling an option pattern for each participant.

*Feasibility and acceptability*. For measuring feasibility, we will use the short version of the Game User Experience Satisfaction scale (GUESS-18 [45];). The scale has 18 items on a 7-point Likert scale (“strongly disagree” to “strongly agree”). It has 9 subscales (with two items each) covering aspects of gaming: usability/playability, narratives, play engrossment, enjoyment, creative freedom, audio aesthetics, personal gratification, social connectivity, and visual aesthetics. We will exclude the subscale “social connectivity” as the game is not a multiplayer game. Scores of different subscales can be added for an overall score. First validity measures show excellent convergent validity, with all subscales above 0.722. Reliability is *α* = .785 for the overall scale. In addition to the GUESS-18, we will analyse the time that was spent on the game and perform sensitivity analyses for drop-outs. The measure will be translated into German by the same procedure as described before.

*Gender*. Gender (in contrast to sex) will be assessed with the Inventar zur Erfassung des Geschlechtsrollen-Selbstkonzepts im Jugendalter (GRI-JUG [46];). This instrument assesses gender identity on four subscales: positive and negative feminine (communal; e.g. “emotional”, “vengeful”) and masculine (agentic; “companionable”, “lazy”) attributes. Each of the subscales consists of 5 items, yielding a total of 20 items. Subjects are asked to rate how much the attributes relate to themselves on a 5-point Likert scale (“does not apply at all” to “applies (nearly) always”). Internal consistencies of the scales are α = .81 (Mas+), *α* = .80 (Mas−), *α* = .88 (Fem+), and *α* = .74 (Fem−). Official English translation of the items exists.

*Gaming experience and preference*. Willingness to engage and hence outcomes might be influenced by gaming experience and gaming preference [47]. The style of the game in this study might remind some participants of games they already played as it is a common style in especially older AGs and some participants might have more experience. We will cover gaming experience with four questions specific to the current study: [1] Do you like videogames (answers are given on a 4-point scale: yes; rather yes, rather no, no)? [2] How much do you play per week (not at all (0 h); little (0–2 h); medium (3–5 h), a lot (more than 5 h))? [3] Have you ever played an adventure game (yes; no)? [4] If yes, what was the name (open question)?.

*Sociodemographic questions and questions to assess potential contamination*. Sex and age will be asked at the beginning of the questionnaires. After the intervention, participants will be shown a screenshot of the intervention game and asked if they have seen this game before. As we cannot gather data of the control game, we will additionally ask for how long the game was played approximately (0-30 min; 30 min–1 h; 1–2 h; more than 2 h). For an overview of the measures, see Table 4.

**Table 4 Tab4:** Measures used in the study

Measure	Assessment tool	Timepoint		
		Pre-test	In-game	Post-test
IER	Vignettes with hypothetical iER situations	x		x
ER	Emotion Regulation of Others and Self scale (EROS; 42)	x		x
Emotional competence	Emotional Skills and Competence Questionnaire (ESCQ; 44)	x		x
IER strategies	In-game option patterns		x	
Gaming experience	Self-developed questions	x		
Gender	Inventar zur Erfassung des Geschlechtsrollen-Selbstkonzepts im Jugendalter (GRI-JUG; 46)	x		
Acceptability	Game User Experience Satisfaction scale (GUESS-18; 45). In-game measures (drop-outs, time)		x	x

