### Participant timeline {13}

This RCT adopts a pre-post-test strategy with the between-participant factor “group” and the within-participant factor “time”. Assessment will include pre-tests (questionnaires; day 1), intervention (playing the game; days 1–5), and post-tests (questionnaires and acceptability measures; days 5–10). After sending the consent forms, every participant will receive the link to the pre-test questionnaires via email. They take approximately  30 minutes to complete. At the end of these questionnaires, participants will be randomly assigned to either experimental or control group and receive the appropriate link for the corresponding game. Additionally, participants are asked to provide a unique identifying code consisting of the first letter of their own first name, the first letter of their mother’s first name, the first letter of their father’s first name, and the day of their birthday. They will use this code in the subsequent parts of the study to allow to link the parts anonymously. The link for the games can be opened as soon as they receive it and accessed with the unique identifying code that they used in the pre-test questionnaires already. Participants are asked to play the game for as long as they want but with the aim to finish it. After that, the participants have 5 days to play the game. They receive the link for post-test questionnaires 5 days after the first link was sent. The post-test questionnaires will take approximately 30 minutes to complete. After 2 days, a generalised reminder is sent to each participant via email to remind them to finish the study if they have not done so already.

The iER AG allows for great variability in playtime, but no matter how long each player takes to finish the game, everyone will have the same amount of iER interactions. As long as they play the game to the end, playtime has no influence on the psychoeducational component but only on the explorative “fun” part of the game. In general, we expect the average playtime to be approximately 3 h in total. The control group will get instructions to play the game as much as they want for the next days. They will receive the final questionnaires 5 days after they started the study. For an overview of the study design, see Fig. 1.

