### Data management {19}

All measures will be administered via online questionnaires at both pre- and post-test via www.soscisurvey.de [38]. This German server is ISO27001 certified and guarantees organisational, structural, and technical security in accordance with current standards. The server is accessed via SSH-encrypted connection. No data is passed on to third parties. No other person has access to the data, in accordance with section 11 of the Federal Data Protection Act. The server uses SSL encryption. Data is already encrypted on the participant’s browser and only decrypted on the server. No IP addresses are stored in the access log files and no cookies are used.

Due to questionnaires being administered online, missing values can be prohibited by not allowing to skip questions. Outcome data will be checked for unrealistic answer patterns (e.g. always the first option).

Outcome data will be stored on secure, password-protected platforms at the Karl Landsteiner University of Health Sciences. Only direct research associates can access the data.

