#### Secondary analyses

*Emotion regulation and emotional competence*. For the two questionnaires about emotion regulation and emotional competence, comparisons between groups will be performed for the pre-test and for the change between pre- and post-test (items change in the Likert scale is set to + 1 or − 1 if the Likert scale improves or worsens, by one point, respectively, and so forth). For both analyses, a Wilcoxon test will be performed.

*Sex differences within the experimental group*. Adaptive iER strategies will be dichotomised into positive engagement vs acceptance and for each participant the more frequent strategy will be determined. Our outcome variable is the proportion of which sex uses positive engagement (or acceptance). A chi-square test will be calculated to compare the percentage between the sexes. Second, a logistic regression analysis will be performed to evaluate if gender stereotype scores have an influence on the more frequent strategy positive engagement or acceptance. Note that for this analysis only adolescents from the experimental group will be considered.

*Feasibility*. Data from the feasibility questionnaire will be analysed using descriptive statistics. Open questions will be analysed qualitatively following thematic analysis [48].

For the secondary and exploratory analyses, the significance level for all tests is set to 0.05, *p*-values are interpreted in a descriptive manner. The statistical software programs R and SPSS will be used [49, 50].

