### Interim analyses {21b}

We do not expect the trial to result in any harmful side effects, and due to online administration, the process will not be monitored. Yet, after an internal pilot phase of 40 participants, we will look at drop-out rates and—if patterns are found during questionnaire completion—possibly change the settings of the online questionnaires to allow participants to skip questions and increase adherence.

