### Methods in analysis to handle protocol non-adherence and any statistical methods to handle missing data {20c}

Missing values will be avoided by not allowing participants to skip questions. Drop-outs will be considered in sensitivity analyses based on the intention-to-treat principle, which means that all participants are considered in the analyses regardless if they completed all questionnaires or not. No data imputation for missing data will be performed.

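### As planned, an experimental-arm child who never opened the game must still rate it on GUESS-18, and those ratings enter the acceptability summary

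*Protocol article*

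**What the plan says.** **Instrument.** Under Secondary outcomes in {18a}, the protocol article states: "For measuring feasibility, we will use the short version of the Game User Experience Satisfaction scale". The scale has 18 seven-point items in nine two-item subscales, "covering aspects of gaming: usability/playability, narratives, play engrossment, enjoyment, creative freedom, audio aesthetics, personal gratification, social connectivity, and visual aesthetics". Social connectivity is dropped because the game is single-player, which leaves 16 items. Table 4 places GUESS-18 at post-test, and lists in-game drop-outs and time beside it as acceptability measures.

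**Timing.** Under Participant timeline {13}: "They receive the link for post-test questionnaires 5 days after the first link was sent". No condition on play is attached. On play itself: "Participants are asked to play the game for as long as they want but with the aim to finish it". The intervention description puts completion at about 3 hours.

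**Response rule.** Under Data management {19}: "missing values can be prohibited by not allowing to skip questions". The missing-data section {20c} repeats it: "Missing values will be avoided by not allowing participants to skip questions". Under Interim analyses {21b}, after a pilot of 40 and depending on the patterns seen, the team may "possibly change the settings of the online questionnaires to allow participants to skip questions and increase adherence".

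**Analysis.** Under Secondary analyses in {20a}: "Data from the feasibility questionnaire will be analysed using descriptive statistics". The main analysis sample, described under Randomisation in {20a}, is everyone whose questionnaires are complete.

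**The concern.** Each rule is reasonable alone. Together they produce ratings with no basis. A child allocated to the adventure game who never opens it still gets the post-test link and the reminder, and has a reason to finish, because the voucher raffle is limited to those who complete the study. To finish, that child must answer items on the story, the sound and the graphics of a game never seen. Those answers look like any others in the data and go into the acceptability summary.

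Feasibility and acceptability form one of the three research questions, and the stated long-term goal is use in Austrian schools. A summary that mixes ratings from players with guesses from children who did not play cannot separate a game that was disliked from one that was not opened. The two would call for different responses. This is a different problem from drop-out, because these children do return and do complete their questionnaires.

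**Working it through.** **1. The plan's own figures.** No GUESS-18 value, target or non-play rate is stated, so there is nothing on this point to reproduce. The sample size does reproduce. With 30% against 10%, two-sided 0.05 and 80% power:

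n = [1.96 × √(2 × 0.20 × 0.80) + 0.84 × √(0.30 × 0.70 + 0.10 × 0.90)]² / 0.20² ≈ 61.6, so 62 per group.

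For drop-out, 124 / 0.70 = 177.1, so 178, against the stated 180. None of this involves GUESS-18.

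**2. Following one child through the stated rules.** Take an experimental-arm child who never opens the game and answers the post-test.

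| Step | Rule in the protocol article | Result |
|---|---|---|
| Is the post-test sent? | Sent 5 days after the first link, {13} | Yes |
| Can GUESS-18 be left blank? | Skipping not allowed, {19} and {20c} | No |
| Is the child in the main sample? | Defined by completed questionnaires, {20a} | Yes |
| Are the ratings left out of the summary? | No restriction under Feasibility, {20a} | No |

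**3. Whether another provision catches this child.**
- Play time is to be analysed in addition to GUESS-18, not as a condition on it.
- The sensitivity analyses in {20c} are for drop-outs, under a principle that keeps in children with incomplete questionnaires. This child's are complete.
- The check for unrealistic answer patterns in {19} gives always choosing the first option as its example. Varied or mid-scale guesses would pass such a check.
- The pilot change in {21b} is conditional and motivated by drop-out. Even if made, it would permit blanks but would not identify children who did not play.
- The self-reported play-time item has 0–30 min as its lowest category, so it merges never opened with briefly played.

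**4. Size.** Let f be the fraction of GUESS-18 respondents who never opened the game, and d the gap between their mean item rating and that of children who opened it. Then

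shift in item mean = f × d; shift in sum = 16 × f × d, with 18 − 2 = 16 items.

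Both f and d are assumptions.

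| f | d (points) | Item mean | 16-item sum |
|---|---|---|---|
| 5% | 1 | 0.05 | 0.8 |
| 10% | 1 | 0.10 | 1.6 |
| 10% | 2 | 0.20 | 3.2 |
| 20% | 1.5 | 0.30 | 4.8 |
| 30% | 2 | 0.60 | 9.6 |

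The sum runs from 16 to 112, so 1.6 points is 1.6 / 96 = 1.7% of its span. With 90 children allocated to the arm and 30% drop-out, about 63 would respond, and f = 10% is about 6 children. The sign of d is unknown: the shift can go either way, and is zero if the guesses average the same as the real ratings.

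**The case against.** The strongest reply is that this is an argument from silence. Survey routing and the denominator of a descriptive summary are details that a journal article may leave to the full protocol or the questionnaire. A ban on skipping displayed questions does not rule out conditional display, and the gaming-experience block already contains a question that applies only after a yes. This stands in part: a filter may exist. But none is described, and the rules that are stated, applied exactly, lead to the result above. The article does restrict the population where it sees the need: the sex-difference analysis is limited to the experimental arm, while the feasibility paragraph has no restriction.

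A second reply is that acceptability is not read from GUESS-18 alone, since Table 4 includes in-game drop-outs and time. This also stands, and softens the consequence: readers will have some information on non-play. It does not take the guessed ratings out of the GUESS-18 summary.

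Several stronger readings are tempting but not supported:
- *Early quitters' ratings are also invalid.* A child who opened the game and left has a real reaction to its usability, look and enjoyment. Only those who never opened it lack a basis for rating.
- *Children are free not to play.* The same sentence in {13} also asks them to aim to finish.
- *Controls must rate a story their puzzle lacks.* The feasibility question concerns the adventure game, and nothing shows that controls rate the puzzle game.
- *The 30% drop-out assumption indicates the non-play rate.* It concerns loss from the study, not non-play among children who return.
- *The mean in particular is distorted.* The article says descriptive statistics, and elsewhere allows a median for skewed data. The same contamination can affect a median.

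**Conclusion.** The point holds for experimental-arm children who never opened the game but complete the post-test. Under the stated rules they must rate it, and their ratings are summarised with the rest. This rests on there being no undescribed filter in the questionnaire and on the no-skip setting staying in force after the pilot.

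The size cannot be established from the documents. At an assumed 10% never opened and a 1-point gap, the shift is 0.1 per item or 1.6 on the 16-item sum, in either direction. The larger rows of the table need fractions and gaps for which the protocol gives no support.

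The reach is limited to one secondary descriptive outcome with no test or stated threshold attached. The point is worth acting on because the remedy is nearly free, and because the filter has to be in the questionnaire before recruitment, which the Trial status section describes as not yet begun.

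**What to change.** 1. In the online post-test, place an option such as 'I did not open the game' before GUESS-18, routing past the scale.
2. Under Secondary outcomes in {18a} and Feasibility in {20a}, state that GUESS-18 is summarised for experimental-arm children whose game log shows that they opened the game. Keep early quitters in, and show results by furthest level reached or by play time.
3. Report the share who never opened the game alongside the play-time and drop-out measures already planned.

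The cost is one survey item and one sentence in each of the two sections. The log is already planned to record choices and start and end times, and the participant code already links the game to the questionnaires. The downside is a slightly smaller denominator for the GUESS-18 summary.

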### Plans to promote participant retention and complete follow-up {18b}

Participants are encouraged to finish the study by raffling 5 Amazon vouchers for 50 Euros between all participants who finish the study. Participants have to enter their email addresses at the end of post-test questionnaires. SoSci Survey allows to handle email addresses for this process independent of the rest of the study to ensure anonymity. Furthermore, a standardised email will be sent to every participant 2 days after sending the post-questionnaire link to remind participants to finish the study if they have not done so already.

